## Abstract

**Background:**

Mental illness has an estimated financial burden on the Danish economy of 3.4% of the gross national product every year due to lost productivity, social benefits, and healthcare costs, and approximately 50% of people receiving long-term sickness benefits have a common mental illness. Furthermore, a significant treatment gap exists where less than 30% are treated for their mental illness. The primary objective of the randomized trial is to examine whether people on sick leave with a diagnosis of anxiety, depression, stress, personality disorders, or functional disorders return to work faster and have higher job retention if they receive an integrated and optimized vocational rehabilitation and mental health care intervention, compared to people who receive the standard mental health care and vocational rehabilitation service.

**Methods:**

The trial is designed as an investigator-initiated, randomized, two-group parallel, assessor-blinded, superior trial. A total of 900 participants with a common mental illness will randomly be assigned into two groups: (1) IBBIS-II, consisting of integrated mental health care and vocational rehabilitation, or (2) service as usual (SAU), at two sites in Denmark. The primary outcome is the difference between the two groups in time to return to work (RTW) at 12 months using data from the Danish Register for Evaluation of Marginalization (DREAM) database.

**Discussion:**

This study will contribute with new knowledge on vocational recovery and integrated vocational and health care interventions in a Scandinavian context.

**Trial registration:**

ClinicalTrials.govNCT04432129. Registered on June 16, 2020

## Administrative information

Note: The numbers in curly brackets in this protocol refer to the SPIRIT checklist item numbers. The order of the items has been modified to group similar items.

## Introduction

### Background and rationale {6a}

Mental illness has an estimated financial burden on the Danish economy of 3.4% of gross national product every year due to lost productivity, social benefits, and healthcare costs and approximately 50% of all people receiving long-term sickness benefits have a common mental disorder. Furthermore, a significant treatment gap exists where less than 30% are treated for their common mental illness [1]. On this basis, the Organization for Economic Co-operation and Development (OECD) has recommended that employment-oriented mental health care should be developed in Denmark, in addition to experimenting with ways to integrate health and employment services [1]. These recommendations, and the sickness benefit reform from 2015, led the Danish Agency for Labour Market and Recruitment (STAR) to launch the “Integrated Employment and Treatment Initiative for Sickness Beneficiaries (IBBIS)” project in 2016. The IBBIS intervention was designed to provide coherent and coordinated mental health care and vocational rehabilitation services to improve the return to work rates for people with stress, depression, and anxiety, and the intervention was evaluated in two randomized controlled trials (RCTs) [2, 3].

As a next step, the initiative was expanded to also provide service to people with personality disorders and functional disorders. The two new groups were selected based on practical knowledge from Jobcenter’s and the literature. A Danish survey showed that the vast majority of people on long-term sick leave suffered from depression or anxiety, but the two following groups were people with somatoform disorders (7%) and personality disorders (5%) [4]. Moreover, a study found that 14% of people with at least 8 weeks of sick leave had a functional disorder [5]. Although personality disorders only account for 5% of people on long-term sick leave, personality disorders develop from early adulthood and have major significance for the ability to work, in addition to a high risk of later onset of anxiety and depression [6].

To include the two new diagnostic groups, the manual-based IBBIS service was revised based on two systematic reviews, as well as drawing on practical experiences gathered from IBBIS-I [7]. Among other things, the vocational rehabilitation service and the organization of the intervention were updated, and the manual was expanded to also include work-related cognitive behavioral treatment (CBT) and treatment for people with personality disorders and functional disorders. The IBBIS-II services are now delivered by Copenhagen and Aarhus municipalities in a collaboration with Psychotherapeutic Clinic, Mental Health Services in the Capital Region of Denmark and Clinical Social Medicine & Rehabilitation, Central Jutland Region, respectively. Due to the extension of two new diagnostic groups and the changes in the delivered services, the effect of the intervention is evaluated in a new RCT which started the inclusion of participants in August 2019. However, due to COVID-19 and the lockdown in Denmark, it was not possible to deliver the IBBIS-II service as intended and complete the study as planned. Because the participants did not receive sufficient support from August 2019 to June 2020, this period was considered as a pilot phase. The present trial started the inclusion of participants in June 2020.

### Objectives {7}

The aim of the randomized trial is to examine whether people on sick leave with a diagnosis of anxiety, depression, stress, personality disorders, and functional disorders return to work faster and have higher job retention if they receive an integrated and optimized vocational rehabilitation and mental health care intervention, compared to people who receive service as usual (SAU), i.e., the standard mental health care and vocational rehabilitation service. The hypothesis is that the IBBIS-II intervention is superior to SAU in return to work (RTW) time at 12 months.

Furthermore, the aim is to include enough participants to analyze whether there are differences in RTW time within the diagnostic subgroup’s depression and stress. We will examine whether these specific subgroups have faster RTW rates and have higher job retention when offered the integrated IBBIS-II intervention compared with participants who receive standard mental health care and vocational rehabilitation.

### Trial design {8}

The trial is designed as an investigator-initiated, randomized, two-group parallel, assessor-blinded, superior trial. Participants in the pilot phase and the main trial will be randomized 1:1 into the two arms of the trial. Only participants in the main trial will be included in the primary analysis.

Figure 1 depicts the flowchart of the trial and the number of participants expected to be included within the groups listed above with a ratio of 1:1 between participants in the two interventions and enough power to examine the effect of the diagnostic subgroup’s depression and stress. The follow-up is only planned through register-based data. The trial will be reported according to the modified CONSORT criteria for non-pharmacological trials [8]

**Fig. 1 Fig1:**
[figure not shown]
Flowchart of the RCT

## Methods: participants, interventions, and outcomes

### Study setting {9}

The interventions will be delivered by a cross-sector and multidisciplinary IBBIS-II team that is organized in collaboration between the mental health services and the vocational services (job centers) in two Danish regions, the Capital Region of Denmark in Copenhagen and the Central Region of Denmark in Aarhus. Participants are referred to the study by a sickness benefit caseworker from the job centers at the two study sites, and the interventions are provided at the job centers.

### Eligibility criteria {10}

All participants must be recipients of sickness benefits and on sick leave from a job or unemployed for a minimum of 4 weeks due to anxiety, depression, stress, personality disorders, or functional disorders.

The following are the inclusion criteria:Anxiety, depression, stress, personality disorder, or functional disorder diagnosed at a structured diagnostic interview based on the Mini-International Neuropsychiatric Interview conducted by the IBBIS team [9].Sickness benefit recipient at baseline; on sick leave from a job or unemployed for a minimum of 4 weeksResident in Copenhagen or Aarhus municipalitiesSpeak sufficient Danish to participate in interviews and complete questionnaires without an interpreterAged ≥ 18 yearsHas given informed written consent

The following are the exclusion criteria:PregnantHigh degree of suicidal ideationDementiaAbuse of alcohol or other drugs to the degree that participation in therapy is not possibleA need for mental health treatment in secondary sector careAn unstable somatic condition that is too severe for participation in the projectParticipation in any psychotherapy or psychotherapy-like treatment outside the IBBIS project, if the participant is randomized to receive the IBBIS intervention

### Who will take informed consent? {26a}

Participants are referred to the IBBIS-II team, by the case worker in the job center, if the general practitioner has stated a mental illness or functional disorder or suspicion thereof or if the participant or the caseworker suspects a mental or functional disorder and the participant has given informed consent to participate in the health assessment. Then, the sickness benefit caseworker at the job center acquires a health professional assessment at the regional IBBIS-II intervention. If the participant meets the criteria for a diagnosis of anxiety, depression, stress, personality disorder, or functional disorder in the health assessment, the participant can be included and randomized in the trial. Before randomization, the participant will be informed orally and in writing about the trial, and assigned informed consent will be attained at the job center. The individual information contains adequate information about the IBBIS-II trial, and the participants are informed that participation in the trial is voluntary, that the trial is not estimated to have any adverse effects, and that they can withdraw from the trial at any time, without consequence for future mental health or employment services.

### Additional consent provisions for collection and use of participant data and biological specimens {26b}

This trial does not involve collecting biological specimens for storage

### Interventions

#### Explanation for the choice of comparators {6b}

We aim to investigate if the IBBIS-II intervention is superior to SAU, i.e., standard mental health care and vocational rehabilitation service. Therefore, we chose to compare the IBBIS-II intervention to SAU alone.

#### Intervention description {11a}

The IBBIS-II service is thoroughly described in the manual and educational material. The service is briefly described below. The IBBIS-II service is delivered by two teams—one in Copenhagen and one in Aarhus. Each team has a team leader and consists of the following:Employment specialists who operate as caseworkers and are employed by job centersCare managers consisting of nurses, occupational therapists, physiotherapists, etc. with experience in mental health care and a minimum of 1 year of training in cognitive behavioral therapyOther healthcare professionals (psychologists, psychiatrists, specialists in social medicine, physiotherapists, and instructors in mindfulness-based stress reduction)

Healthcare professionals are employed by the two collaborating regions, and employment specialists are employed by the job centers in the two municipalities. Care managers have a maximum momentary caseload of 25, and employment specialists have a maximum momentary caseload of 30.

The entire staff has received training in the IBBIS-II service prior to the initiation of the study, and the employment specialists and care managers receive ongoing supervision.

The IBBIS-II services have the following core elements:AssessmentAll participants referred to the service receive a mental health assessment.Planned integrated serviceThe participant has the same employment specialists and care manager throughout the intervention.A joint plan is made with shared decisions between the participant, the employment specialist, and the care manager.There is a focus on disclosure (openness about illness) and involvement of relatives and significant others.Vocational rehabilitationFocus on RTW with ongoing assessment of job goals, competencies, and need of support.Participants receive help in contacting existing employers (employed) and potential employers (unemployed).Unemployed participants are offered an individualized job search effort.The focus is on competitive jobs within the community.The treatmentIs based on stepped care and uses structured treatment guidelines. The stepped care includes the following:i.Psychoeducationii.Work-related cognitive behavioral therapy for depression and anxiety disorders and special stress interventions for stress and stress-related disordersiii.Psychotherapy, physiotherapy, and medical treatmentOngoing supportWhen the participant has obtained work the team continues to offer support.

#### Service as usual (SAU)

The control group receives SAU, i.e., the treatment and employment interventions that are usually offered to citizens who are on sick leave due to depression, anxiety, stress, personality disorders, and functional disorders in the regions and municipalities where IBBIS-II is being tested.

#### Criteria for discontinuing or modifying allocated interventions {11b}

There will be no specific criteria for discontinuing or modifying allocated interventions.

#### Strategies to improve adherence to interventions {11c}

The IBBIS-II team delivers the intervention IBBIS-II mental health care integrated with IBBIS-II vocational rehabilitation. The interventions are carried out with emphasis on participant involvement through shared decision-making to improve participant satisfaction [10] and involvement of the participants’ relatives. Continuously, adherence to intervention protocol is monitored. A fidelity scale is developed and used for biannual fidelity reviews to ensure program adherence and continuous focus on program implementation and improvement.

#### Relevant concomitant care permitted or prohibited during the trial {11d}

Participation in any psychotherapy or psychotherapy-like treatment outside the IBBIS-II project is unwanted during the trial if the participant is randomized to receive the IBBIS intervention.

#### Provisions for post-trial care {30}

There is no anticipated harm and compensation for trial participation

	Questionnaire	Level of Personality Functioning Scale – Brief Form (LPFS-BF) 2.0	X		
	Questionnaire	Common Mental Disorders Questionnaire (CMSQ), Questions 1-19	X		
	Questionnaire	Level of functioning measured with the Sheehan Disability Scale (SDS)	X		
	Questionnaire	Return to work self-efficacy (RTW-SE)	X		
	Questionnaire	Disability management self-efficacy measured with University of Washington Self-Efficacy Scale (UW-SES)	X		
	Questionnaire	The Quality of Life Scale (QOLS)	X		
	Questionnaire	Health-related quality of life measured with EQ-5D-5L	X		

*RTW* return to work

#### Participant timeline {13}

The participant timeline is shown in Fig. 1.

#### Sample size {14}

Based on a sample size calculation, 900 participants must be included in the trial. On the assumption that even a few weeks’ differences in work per year can have a relevant economic significance, we choose to apply a conservative estimate of a relevant difference between the control and intervention group with a HR of 1.5. The number of days before returning to work is also conservatively estimated at 300 days. With an inclusion period of 1 year and 11 months (700 days), a follow-up time of 365 days, and a 1:1 ratio in the two arms of the trial, a total of 900 participants should be included, to reject the null hypothesis that the time to work of the experimental and control groups is equal with a probability (power) of 94% and a type I error of 0.05. With the inclusion of 900 participants, it is possible with sufficient power (0.94) to examine a HR of 1.25 relative to the two main arms of the trial. A total of 358 participants should be included in each of the subgroups of depression and stress, to reject the null hypothesis that the time to work of the experimental and control groups is equal with a probability (power) of 88% and a type I error of 0.05. The results from the pilot study of IBBIS-II showed that it is unlikely to include enough participants in subgroups of anxiety, personality disorder, and functional disorder to conduct subgroup analyses with enough power.

Power estimation of the secondary outcome, proportion in competitive employment during the 12-month follow-up period, shows that a clinically relevant significant difference of 15% (60% vs. 75%) can be detected with power very close to 1.00, if 450 participants are included in each group. When comparing subgroups, a clinically relevant difference of 15% can be detected with a power of 0.8, if 151 participants are included in each group, meaning that it is likely that there is sufficient power in the depression and stress subgroups to detect relevant differences in employment rates.

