### Data collection and management

#### Plans for assessment and collection of outcomes {18a}

The participants will be followed up at 6 and 12 months using register-based data. The primary, secondary, and explorative outcomes are presented in Table 1. The primary outcome is RTW measured by time to RTW from baseline until 12 months after baseline using register-based employment data (DREAM database). Time to RTW is defined as a minimum of 4 weeks of continuous work without receiving sickness benefits. The secondary outcome is the proportion of unsupported competitive employment at 12 months follow-up using DREAM data. Explorative outcomes include measures of labor market attachment using DREAM data and electronic income data, as well as primary and secondary healthcare using health care data from the National Danish registers (Table 1). The Four-Dimensional Symptom Questionnaire (4DSQ) is a 50-item questionnaire designed to assess self-reported common psychological symptoms in the last week and has a special focus on distinguishing general distress from depression, anxiety, and somatization [15]. The Work and Social Adjustment Scale (WSAS) [16] is a simple, reliable, five-item scale that measures functional impairment related to an identified problem, which is defined in this trial as psychological symptoms. The Karolinska Exhaustion Scale (KES) 26-item version measures the degree of exhaustion disorder and the four interrelated dimensions of exhaustion disorder according to the Swedish National Board of Health and Welfare: lack of recovery, cognitive exhaustion, somatic symptoms, and emotional distress [17]. The Level of Personality Functioning Scale – Brief Form (LPFS-BF) 2.0 measures impairment in personality functioning [12]. The Common Mental Disorders Questionnaire (CMDQ), questions 1–19, is covering symptoms and signs commonly associated with somatoform disorders and worries about health validated as a diagnostic aid in primary care settings [13]. The Sheehan Disability Scale (SDS) measures functional impairment in three inter-related domains: work/school, social life, and family life [18, 19]. Return to work self-efficacy (RTW-SE) is an 11-item measure for self-efficacy beliefs regarding return to work where respondents are asked to respond to statements about their jobs, imagining that they would start working tomorrow in their present emotional state [20]. The 17 items University of Washington Self-Efficacy Scale (UW-SES) measure self-efficacy and is validated across diagnostic conditions [21]. The Flanagan QOLS is a 16-item instrument that measures 5 conceptual domains of quality of life: material and physical well-being; relationships with other people; social, community, and civic activities; personal development and fulfillment; recreation; and independence [22]. The EQ-5D-5L is a measure of health status in five domains: mobility, self-care, usual activities, pain/discomfort, and anxiety/depression and also includes a visual analog scale from 0 (worst imaginable health status) to 100 (best imaginable health status) [23].

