## Discussion

This paper describes the study protocol of a randomized controlled trial comparing (1) IBBIS-II intervention with (2) SAU, i.e., standard mental health care and standard vocational rehabilitation for people on sick leave because of depression, anxiety, personality disorders, or functional disorders. Common mental disorders are frequent causes of sick leave with a great cost for the individual and society. The IBBIS-II trial will test the effect of an integrated health care and vocational rehabilitation intervention to reduce the burden of depression, anxiety, personality disorders, or functional disorders.

This randomized controlled trial is designed with great emphasis on minimizing bias, and reporting is done in accordance with the SPIRIT guidelines [24]. This study has several methodological strengths, including (1) the sample size is large, and hence, we expect high statistical power, which allows for the detection of relevant differences in both primary and secondary outcomes; (2) the randomization is done in accordance with high methodological standards; and (3) the primary outcome is based on register data, and we thus expect complete data on return to work and to avoid the common biases resulting from self-assessed data such as recall bias.

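### The sample size section gives 94% power with 900 participants at both HR 1.5 and HR 1.25; with 12-month follow-up, power at HR 1.25 is about 68–82%

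*Protocol article*

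**What the plan says.** All of the power figures are in the Sample size section of the protocol article. It takes "a conservative estimate of a relevant difference between the control and intervention group with a HR of 1.5" as the design effect and 300 days as the time to return to work (RTW). It does not say whether 300 days is a mean or a median, or which arm it describes. It continues: "With an inclusion period of 1 year and 11 months (700 days), a follow-up time of 365 days", 1:1 allocation and a type I error of 0.05. From these inputs it arrives at 900 participants. The stated purpose of that number is "to reject the null hypothesis that the time to work of the experimental and control groups is equal with a probability (power) of 94" per cent.

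The next sentence adds that, for the same sample size, "it is possible with sufficient power (0.94) to examine a HR of 1.25 relative to the two main arms of the trial". Then: "A total of 358 participants should be included in each of the subgroups of depression and stress", with 88% power and no HR beside it.

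The section on assessment and collection of outcomes defines the primary outcome as "time to RTW from baseline until 12 months after baseline", and the statistical methods section also uses a 12-month window. The Discussion lists power among the trial's strengths: "the sample size is large, and hence, we expect high statistical power".

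**The concern.** For a fixed number of participants and a fixed test, power rises steeply with the effect size. Ln 1.5 is 0.405 and ln 1.25 is 0.223, so the same 900 people cannot give 94% power at both. At least one of the two statements must be wrong.

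The follow-up inputs raise a second question. In a standard time-to-event calculation, an inclusion period adds events only if early entrants are followed beyond the minimum follow-up time. This trial stops counting at 12 months for everyone.

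At stake is the type II error that readers attach to the primary analysis. Power of 94% at HR 1.25 means a 6% chance of missing that effect; power of 68–82% means an 18–32% chance.

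**Working it through.** **Inputs from the document.** N = 900 in total (450 per arm); HR 1.5 and HR 1.25; type I error 0.05; 300 days to RTW; 700 days of inclusion; 365 days of follow-up; follow-up expected to be nearly complete, so no dropout.

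**Assumptions.** The test is two-sided: the null hypothesis is equality, the stated aim is to test for a difference, and a 95% confidence interval is reported. RTW times are exponential. The 300 days is read in turn as a median or a mean, and as belonging to the control arm, the intervention arm, or the geometric middle of the two.

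**Formula (Schoenfeld, 1:1).** Power = Φ(½·√d·|ln HR| − z), where d is the number of events and z = 1.960.

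**1. Ceiling at HR 1.25, which needs no assumption on timing.** Events for 94% power: 4 × ((1.960 + 1.555)/0.2231)² ≈ 993. If all 900 participants had the event: ½ × 30 × 0.2231 − 1.960 = 1.387, so power is 0.917 (0.915 by Freedman's formula).

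**2. Attempt to reproduce 94% by letting the 700 days add follow-up.** With uniform accrual over A = 700 days and follow-up to F = 365 days after the last entry, the event probability is 1 − [exp(−λF) − exp(−λ(A+F))]/(λA). At HR 1.25 this gives 737 events and power 0.857 (control median 300), or 817 events and 0.890 (control mean 300). At HR 1.5 power is 0.99 or more. The figure of 94% is not reproduced at either HR.

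**3. The design as defined: 365 days from baseline for everyone.** With a control median of 300 days, the 12-month RTW probability is:
- control: 1 − exp(−0.6931 × 365/300) = 0.570
- intervention at HR 1.25: 0.652
- intervention at HR 1.5: 0.718

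HR 1.25: d = 450 × (0.570 + 0.652) ≈ 550, and ½ × √550 × 0.2231 − 1.960 ≈ 0.656, so power is 0.744 (Freedman 0.740).

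HR 1.5: d = 450 × (0.570 + 0.718) ≈ 579, so power is 0.998.

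Two-sided power over the readings of 300 days, fixed 365-day follow-up:

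| Reading of 300 days | N = 900, HR 1.25 | N = 900, HR 1.5 | N = 358, HR 1.5 | N = 358, HR 1.25 |
|---|---|---|---|---|
| Median, intervention arm | 0.68 | 0.99 | 0.77 | 0.34 |
| Median, control arm | 0.74 | 0.998 | 0.87 | 0.38 |
| Mean, control arm | 0.82 | over 0.99 | 0.92 | 0.44 |

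The other readings fall between the first and last rows.

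**4. Cross-check.** The protocol's 60% and 75% employment rates belong to the secondary outcome. Used as a rough proxy for the event share, they give 450 × (0.60 + 0.75) ≈ 607 events and power of about 0.785 at HR 1.25, inside the range above.

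**5. One-sided 0.05.** The ceiling at 900 events rises to 0.956, and 94% would need 823 events. With fixed 12-month follow-up, power at HR 1.25 is 0.834 (control median) or 0.892 (control mean), the highest of any reading.

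**The case against.** The strongest defence is that sidedness is not stated. A one-sided 0.05 test, with 300 days as the control mean and the 700-day inclusion period adding follow-up to study end, gives 0.939 at HR 1.25, which matches the printed figure. A reader might also go too far the other way and call 94% impossible on any reading; the document does not support that, because the ceiling of 91.7% depends on two-sided testing, which is only implied. The defence still fails. It conflicts with the equality null and the 95% interval, and it needs follow-up beyond the 12 months that define the outcome. It leaves the same 94% at HR 1.5 unexplained. It does not give 88% for 358 participants either (0.979 at HR 1.5).

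Three other inferences are tempting and should not be made.

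- **Origin of the figure.** 358 participants at HR 1.5, with a control median of 300 days and 700 + 365 days, give 301 events and power of 0.940. A reader might conclude that the 94% was carried over from that calculation. One numerical match does not establish this, and the document says nothing of it.
- **Subgroups.** A reader might infer that the protocol claims power for HR 1.25 in depression and stress. It does not: the HR 1.25 sentence is limited to the two main arms, and the 88% is most naturally read at HR 1.5. The missing HR is a matter of clarity.
- **Interpretation of a null result.** A reader might infer that a non-significant result will be taken as evidence of no effect. The protocol does not say so, and it will report the HR with a 95% interval, which shows the precision.

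It also stands that the trial is amply powered for its declared design effect, HR 1.5.

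**Conclusion.** Wrong as written. The two 94% statements cannot both hold, and under two-sided 0.05 with 12-month follow-up neither does: power is at least 99% at HR 1.5 and about 68–82% at HR 1.25. Within that range, 74% applies if 300 days is the control median and 82% if it is the control mean. No single value can be fixed until the meaning of 300 days is stated. The range rests on exponential RTW times and near-complete follow-up. The conclusion that HR 1.25 falls short of 94% is firmer: with 900 in total and a 12-month window, even a one-sided test stays at or below about 89%.

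For subgroups of 358, the stated 88% is compatible with HR 1.5 (77–92% with fixed follow-up) and not with HR 1.25 (34–44%).

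**What to change.** Restate the paragraph for 900 participants, each followed for 365 days from baseline:

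- Power of at least 99% for HR 1.5 and about 68–82% for HR 1.25, narrowed to one value once 300 days is defined by type (mean or median) and arm.
- The sidedness of the 0.05 level.
- The expected number of events: about 550 at HR 1.25 and 580 at HR 1.5 if 300 days is the control median.
- Remove the claim that power is sufficient, at 0.94, for HR 1.25.
- Keep the 700-day inclusion period from adding follow-up beyond 12 months in the calculation.
- State that the 88% for the 358-participant subgroups refers to HR 1.5 (about 77–92% with fixed follow-up, depending on what 300 days means), and that power there at HR 1.25 would be only about 34–44%.

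The Trial status section reports that recruitment closed with 900 included. No extra enrolment follows from this point, and no outcome or analysis changes. The cost is wording, and the stated power for HR 1.25 becomes less favourable.
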